## Abstract

**Background:**

Efforts to improve HIV diagnosis and antiretroviral therapy (ART) initiation among people living with HIV and reduce onward transmission of HIV rely on innovative interventions along multiple steps of the HIV care continuum. These innovative methods are particularly important for key populations, including men who have sex with men (MSM) and transgender women (TW). The HIV epidemic in Myanmar is concentrated among key populations, and national efforts now focus on reducing stigma and improving engagement of MSM and TW in HIV prevention and care.

**Objective:**

This study aims to test the use of several innovations to address losses in the HIV care continuum: (1) use of respondent-driven sampling (RDS) to reach and engage MSM and TW in HIV testing, (2) HIV self-testing (HIVST) to increase HIV testing uptake and aid early diagnosis of infection, (3) community-based CD4 point-of-care (POC) technology to rapidly stage HIV disease for those who are HIV infected, and (4) peer navigation support to increase successful health system navigation for HIV-infected MSM and TW in need of ART or HIV engagement in care.

**Methods:**

To assess the effect of HIVST, we will implement a randomized trial in which MSM and TW adults in the greater Yangon metropolitan area who are HIV uninfected will be recruited via RDS (N=366). Participants will complete a baseline socio-behavioral survey and will be randomized to standard, voluntary counseling and testing (VCT) or to HIVST. Biologic specimens will be collected during this baseline visit for confirmatory testing using dried blood spots. Participants will be asked to return to the study office to complete a second study visit in which they will report their HIV test result and answer questions on the acceptability of the assigned testing method. Aim 1 participants with confirmed HIV infection and who are not engaged in care (N=49) will be offered direct enrollment into Aims 2 and 3, which include immediate CD4 POC and the option for peer navigation, respectively. Aims 2 and 3 participants will be prospectively followed for 12 months with data collection including interviewer-administered sociobehavioral survey, CD4 POC, and viral load testing occurring biannually. Participants who accept peer navigation will be compared to those who decline peer navigation. Analyses will estimate the impact of CD4 POC on engagement in care and the impact of peer navigation on ART adherence and viral load.

**Results:**

Formative qualitative research was conducted in June and September 2015 and led to further refinement of recruitment methods, HIVST instructions and counseling, and peer navigation methods. Aim 1 recruitment began in November 2015 with subsequent enrollment into Aims 2 and 3 and is currently ongoing.

**Conclusions:**

These innovative interventions may resolve gaps in the HIV care continuum among MSM and TW and future implementation may aid in curbing the HIV epidemic among MSM and TW in Myanmar.

## Introduction

Efforts at both international and national levels have been re-energized toward ending the HIV epidemics. The United Nations and national strategies now focus on increased testing for the identification of previously undiagnosed HIV infection for linkage to care and treatment engagement [1]. Since the HIV Prevention Trials Network (HPTN) study 052 highlighted the preventive benefits of early antiretroviral therapy (ART) treatment [2], most countries have adapted their treatment criteria to initiate treatment at CD4 <500 cells/µL, in accordance with 2013 World Health Organization (WHO) guidelines, while some countries have begun adopting the 2015 WHO guidelines of providing treatment for all people living with HIV [3]. The majority of these global efforts focus on the general populations, although for settings where HIV is concentrated among key populations, such as gay men and other men who have sex with men (MSM), transgender women (TW), sex workers, and people who use drugs, it is imperative to ensure that access to treatment and care is available for key populations in order to have true impact on the epidemic trajectories [4,5].

Achieving such goals for MSM and TW is challenging given contexts of stigma, discrimination, and criminalization and require innovative approaches to overcoming these challenges and engaging these populations in HIV testing and care. Considering the HIV care continuum (Figure 1), these innovative approaches can be viewed in terms of several stages for MSM and TW: (1) initial contact with or outreach to MSM and TW, (2) HIV testing and diagnosis, (3) HIV staging according to national criteria, (4) engagement and retention in care, (5) treatment initiation, and (6) viral load suppression.

A long-standing approach to reaching MSM and TW has been the use of mobile and other forms of street or venue-based outreach to engage these populations in HIV testing. These methods assume at-risk members of the population are present in sites accessible to outreach workers and often result in frequent retesting of the same individuals. Respondent-driven sampling (RDS), however, has become popular in the last decade as an alternative sampling method that can effectively penetrate deep into social networks of key populations and recruit a more representative sample [6,7]. RDS is a peer-based recruitment method that has been developed as a nonprobability sampling approach for surveys of hidden and stigmatized populations [8]. It has shown benefit in reaching individuals who may not be present at venues or who frequent health facilities less often [9]. As such, RDS may have a role beyond research in engaging MSM and TW in HIV testing and other HIV prevention and care interventions, particularly in settings of stigmatization and criminalization [10-12].

Self- or home-based HIV testing (HIVST) has also emerged as an important tool to promote HIV screening and, potentially, to increase frequency of HIV testing among key populations for whom more frequent testing is recommended [13]. Salivary-based HIV self-test kits have been approved by the US Food and Drug Administration (FDA) and are commercially available in the United States [14]. They have also been increasingly used in research and programs in developing countries as an alternative to facility-based testing [15]. One of the most beneficial aspects of HIVST is its empowerment of individuals to take control of their own health and HIV prevention or care while allowing users to test at their own convenience and in the privacy of their own home or setting of their choice.

A systematic review and meta-analysis of supervised and unsupervised HIVST in both low- and high-risk populations found that self-testing was highly acceptable, preferred by persons at high risk for HIV, and was more likely than clinic-based testing to result in partner HIV testing [15]. Self-testing has the potential to overcome the barriers experienced by MSM and TW as it relates to HIV testing uptake by placing the locus of control on the individual, increasing confidentiality, and allowing members of stigmatized groups to test in settings of privacy, safety, and dignity [16]. HIV rapid tests have grown more sensitive and less complex, making self-testing a viable alternative to clinic-based testing.

**Figure 1 figure1:**
[figure not shown]
HIV care continuum among people living with HIV.

Beyond HIV diagnosis, there is considerable evidence that a major loss of HIV-infected persons in the treatment continuum occurs during disease staging [17]. In most settings, seeking and receiving clinical staging and CD4 testing is required for initiation of ART and generally requires visits to additional facilities where CD4 testing is available. This is often accompanied by long waiting times for results, concerns of unintentional disclosure of sexual or gender identity and disease status to others, and additional steps after staging to link patients to ART [18-20]. These issues around the availability of CD4 testing are common causes of losses at this critical step in the continuum.

Further, there are multiple challenges to successful navigation of the health care system, including but not limited to discrimination and stigma in health care settings. Recently, peer-navigation has been increasingly used among MSM and TW and other key populations to support navigation through a complex system of care, retention in care, and treatment adherence [21-23]. Peer navigators further provide health and HIV information and social support when coping with diagnosis, dual stigmatization of HIV and sexual or gender identity, and disclosure [21-23].

All of these challenges in the HIV care continuum are relevant in Myanmar (formerly known as Burma) and particularly so for MSM and TW populations in the country. Since the early 1990s, the HIV epidemic in the country has seen high rates of morbidity and mortality, very low access to ART, and limited and problematic HIV surveillance and reporting [24,25]. Further, the epidemic has disproportionately affected several key populations in Myanmar, including MSM and TW. While HIV rates appear to have declined among the general population, what limited data are available on key populations suggest that HIV remains concentrated in these groups, disease burdens are high, and access to voluntary counseling and testing services, prevention, and HIV treatment and care remain elusive to many [26,27]. The most recent Joint United Nations Program on HIV/AIDS and Ministry of Health report estimates that some 11.6% of the estimated 230,000 MSM and TW in Myanmar are living with HIV, with prevalence as high as 26.6% among MSM and TW in Yangon, compared to 0.53% of reproductive aged adults [28,29]. With approximately 53% estimated to be reached by prevention services and 20% reached with HIV testing, the same report highlights the need for programs that can reach MSM and TW who are not openly gay and do not seek services [28].

Barriers to HIV care have been common and chronic issues in Myanmar [26]. CD4 criterion for ART initiation in Myanmar is 350 cells/µL, and until 2014, when ART availability was limited, priority was given to patients with CD4 count below 150 cells/µL [30]. The median actual starting level of CD4 in 2012 in Myanmar was 60 cells/µL [26]. National guidelines also recommend treatment initiation at CD4 <500 cells/µL for coinfected patients and for patients from key affected populations, such as MSM and TW [31]. Recent increases in treatment access as a result of support from United States President's Emergency Plan for AIDS Relief (PEPFAR), the Three Millennium Development Goals Fund (3 MDG, a joint donor fund established in Myanmar before the Global Fund began activities in the country), the Global Fund, and the World Bank have led the National AIDS Program to estimate the availability of at least 50,000 new treatment slots in Myanmar in the next 2 years [28]. MSM and TW in Myanmar, and in many settings, are more likely to have undiagnosed HIV infection, since the stigma and discrimination they face in the community, wider society, and in health care settings can be a barrier to testing, disclosure, and seeking health care overall [32].

The primary aim of the Parasol study is to use the overarching framework of the HIV care continuum [17] to measure and overcome barriers to HIV testing and access to care through a series of 4 primary innovations for MSM and TW in Myanmar. We propose to test the following innovations to address losses in the HIV care continuum: use of RDS to reach and engage MSM and TW in HIV testing, HIV self-testing to increase testing uptake, staging of HIV disease for those who are infected through CD4 point-of-care (POC) technology [33,34], and training and capacity building of a cadre of peer health navigators for MSM and TW to increase successful health system navigation for HIV-infected MSM and TW in need of ART or HIV engagement in care [22,23,34]. Longer-term engagement in care will be assessed through the current gold standard for HIV treatment: successful HIV viral suppression as measured by quantitative viral load at 12 months posttreatment initiation [35].

## Methods

### Study Design

This study is conducted in a staged process, beginning with a qualitative, formative phase that is intended to inform further development of recruitment and intervention methodologies, followed by a 3-step continuum interventions study in Yangon, Myanmar. Specific aims and hypotheses are dedicated to each step along the continuum from engagement in HIV testing through RDS and evaluation of HIVST (Aim 1), evaluation of CD4 POC staging (Aim 2), and assessment of peer navigation for treatment initiation and adherence support (Aim 3). This manuscript describes the methodology for the continuum interventions study (qualitative methods have been described elsewhere) [36]. The participant flow diagram displays the study flow, randomization point, and target sample size (Figure 2).

**Figure 2 figure2:**
[figure not shown]
Participant flow diagram.

### Study Site

The study is conducted in Yangon, Myanmar. Yangon, formerly the capital of Myanmar, remains an important urban center and is the largest city in Myanmar with a population exceeding 7.3 million persons in 2014 [37]. There is growing recognition and acceptance of the lesbian, gay, bisexual, and transgender (LGBT) populations in Yangon and a substantial emergence of community-based HIV prevention and care services for MSM and TW within the city.

### Aim 1: HIV Self-Testing Versus Clinic-Based Testing

To assess the effect of HIVST, we have designed a randomized trial in which MSM and TW adults in the greater Yangon metropolitan area will be recruited through RDS and offered HIV testing. Participants are randomized to receive standard clinic-based voluntary counseling and testing (VCT) or the HIVST intervention.

#### Aim 1 Study Sample

Aim 1 participants are included on the basis of the following inclusion criteria: assigned male sex at birth, aged 18 years or older, reports having had any type of sex with another man in the past 12 months, presents to the study with a valid RDS coupon (except seeds), speaks Myanmar, currently a resident of the greater Yangon area, is mentally sound and capable of providing consent to participate, and has provided informed consent to participate in the study. Participants who have been tested for HIV within the last 6 months or who are known to be living with HIV infection are excluded from participation in Aim 1. However, individuals who disclose a positive HIV status when Aim 1 eligibility is determined are considered for enrollment in Aims 2 and 3, provided they meet all eligibility criteria for those aims. While there are emerging and increasingly open gay communities in Yangon, the traditional categories of sexual orientation and gender identity in Myanmar culture are blurred; locally, the term MSM is often used interchangeably across male and transgender-identified populations and these groups often attend similar community-based events [38]. Thus, this study focused on the inclusion of both MSM and TW populations.

The target sample size needed for the RDS sample is 366 MSM and TW participants. This estimate achieves 2 goals. First, it allows for a comparison of HIVST versus clinic-based HIV testing. Assuming an error of .05 and 80% power to detect a 15% difference in acceptability between the 2 testing methods (60% acceptability of clinic-based testing and 75% acceptability of self-testing), a sample of 330 (or 165 per group) is needed. Upon factoring a 10% nonresponse in both testing methods, an effective sample size of 366 MSM and TW participants is calculated. Second, this allows for subsequent enrollment of MSM and TW participants into Aims 2 and 3. Assuming a conservative 15% prevalence of HIV among the sample [28], this identifies 54 participants who are then eligible for Aims 2 and 3.

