#### Aims 2 and 3 Recruitment

Participants who test positive during Aim 1 or who report a previous diagnosis of HIV infection are offered enrollment by the study team into Aims 2 and 3. Separate consent forms are provided for each of these aims. Specifically, the consent form for Aim 2 requests consent to participate in CD4 POC testing, and the consent form for Aim 3 will request consent for participation in peer navigation.

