#### Aims 2 and 3 Study Sample

Inclusion criteria for Aims 2 and 3 are assigned male gender at birth, aged 18 years or older, reports having had any type of sex with another man in the past 12 months, is mentally sound and capable of providing consent to participate, speaks Myanmar, current resident of the greater Yangon area, diagnosed with HIV infection, not currently engaged in any treatment or care programs, and has provided informed consent to participate in the study. Participants will be excluded from Aims 2 and 3 if they report that they are already linked into an HIV treatment or care program or have tested negative for HIV infection.

The overall study sample size estimate was driven by the numbers needed for the feasibility and acceptability studies of CD4 POC testing, viral load, and peer navigation, with a target of 54 participants in CD4 POC testing to assess key parameters. Assuming a 10% decline in participation for peer navigation and viral load testing, our target sample for viral load and peer navigation is 49 participants. As data analysis and monitoring are ongoing during data collection, RDS can be extended for additional recruitment should additional recruitment be required to reach targets in Aims 2 or 3. Further, if necessary to reach our desired Aim 2 sample size, additional MSM and TW who are newly HIV-diagnosed can be recruited from partnering organizations for this phase.

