#### Aims 2 and 3 Data Collection

Upon determination of eligibility and verbal confirmation of informed consent, participants complete a structured 20-minute interviewer-administered questionnaire. Participants are then asked to return to participate in surveys conducted at 6 and 12 months. Surveys assess the primary outcome and initiation of ART as well as ART adherence (among those successfully initiated) and other clinical outcomes, including viral suppression, as measured by HIV viral load assessment at 0, 6, and 12 months. This questionnaire is used to assess the strength of peer navigation in improving access and uptake of viral load by MSM and TW living with HIV in care. Peer navigation implementation data (eg, number of meetings per participant, types of support provided) along with participant perceptions will be collected to understand the benefits and challenges of peer navigation and note opportunities for improvement. Incentives are distributed at the conclusion of each follow-up survey. An electronic data entry and tracking system has been developed for this study and allows for registration, screening, survey data collection, data entry of laboratory results, and participant tracking through a secure, Health Insurance Portability and Accountability Act–compliant site. This system is used throughout all phases of the study (Figures 4 and 5).

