All surveys are interviewer-administered and collected using secure, computer-based systems. Anonymous, paper-based surveys are used only as back-up to the computer-based systems. Any anonymous, paper-based data collection forms are secured in a locked cabinet in the project offices. Data entry will take place at the study office, where study data are maintained on designated password-protected computers. Electronic transfer from the study office to JHU occurs only through encrypted files. The JHU principal investigator (CB) and in-country principal investigator (SN) control access to the data. Only relevant study staff who have completed ethical training and have permission from the principal investigator have access to the data.

Following completion of study activities, eligible participants receive 9000 kyat (about US $7) at visit 1 as incentive and reimbursement of travel costs to the project office. Participants who are ineligible at visit 1 also receive 1000 kyat (about US $0.80) for travel expenses. Participants are provided with another 5000 kyat (US $4) at visit 2 for travel expenses as well as an additional 1000 kyat (about US $0.80) for each RDS recruitee who is eligible and participates in the study (maximum of 3 recruitees). These incentive amounts are consistent with other RDS studies implemented in Myanmar and are determined to encourage recruitment without unduly coercing participation [51]. For eligible participants, subsequent visits at 6 and 12 months upon enrollment into Aims 2 and 3 include 10,000 kyat (about US $8) as incentive and to cover travel expenses.

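### Prior diagnosis and current care are known only from self-report under a pay incentive, and no stated rule uses the month-0 viral load to separate participants already suppressed at entry

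*Protocol article*

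**What the plan says.** **Screening.** Under Aim 1 Study Sample, "Participants who have been tested for HIV within the last 6 months or who are known to be living with HIV infection are excluded" from Aim 1. The only route by which known status is described as coming to light is the participant's statement: "individuals who disclose a positive HIV status when Aim 1 eligibility is determined are considered for enrollment in Aims 2 and 3". Under Aims 2 and 3 Study Sample, "Participants will be excluded from Aims 2 and 3 if they report that they are already linked into an HIV treatment or care program". The article describes no record check or other objective check of either condition.

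**Entry to Aims 2 and 3.** Under Aims 2 and 3 Recruitment, "Participants who test positive during Aim 1 or who report a previous diagnosis of HIV infection are offered enrollment". A new diagnosis is thus not required; not being in care is.

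**Payment.** Under Human Subjects Considerations, "eligible participants receive 9000 kyat (about US $7) at visit 1 as incentive and reimbursement of travel costs to the project office". By contrast, "Participants who are ineligible at visit 1 also receive 1000 kyat (about US $0.80) for travel expenses". Then "Participants are provided with another 5000 kyat (US $4) at visit 2 for travel expenses", plus 1,000 kyat per eligible recruit up to three, and 10,000 kyat for the 6- and 12-month visits of Aims 2 and 3.

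**Outcomes.** Aims 2 and 3 Analytical Approach lists, among its primary outcomes, the numbers who start ART and who reach viral suppression. Aim 3 compares accepters with decliners of peer navigation without randomization. Aims 2 and 3 Data Collection has suppression "as measured by HIV viral load assessment at 0, 6, and 12 months", so an entry value exists. No stated rule uses it to separate people who arrive already suppressed.

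**The concern.** A person in HIV care who discloses this is ineligible for Aim 1 (known positive) and for Aims 2 and 3 (in care). The same person who stays silent is eligible for Aim 1 and, after a positive dried blood spot, can be offered Aims 2 and 3. The payment difference favors silence, and it is largest for those already in care, because disclosure leaves them no other way in. The recruiter is also paid only for an eligible recruit. The article itself names stigma and fear of disclosure as barriers, which are further reasons not to tell.

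If such people enter, two results are affected. Counts of ART initiation and suppression would include treatment and suppression that predate the study. The Aim 3 contrast would mix the effect of navigation with treatment already under way, in proportions that may differ between accepters and decliners.

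**Working it through.** **1. The plan's own figures.** Assumed prevalence is 15% of 366: 0.15 × 366 = 54.9, stated as 54. A 10% decline gives 54 × 0.9 = 48.6, stated as 49. Both reproduce within rounding, and this point does not change them.

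**2. Payment** (Human Subjects Considerations).
- Visit 1: 9,000 if eligible against 1,000 if not, a ratio of 9 and a difference of 8,000 kyat.
- All of Aim 1: 9,000 + 5,000 + 3 × 1,000 = 17,000 kyat at most.
- With Aims 2 and 3, if 10,000 is paid at each of two visits: 17,000 + 2 × 10,000 = 37,000 kyat at most.

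**3. Effect on overall suppression.** The share of concealed, already treated participants is not in the document, so everything here is assumed. Let n = 49, k the number concealed, s = 90% the suppression among them, and p the suppression among everyone else. Observed suppression is [(n − k)p + ks]/n, so the overstatement is k(s − p)/n.

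| Concealed share (k) | p = 40% | p = 60% | p = 80% |
|---|---|---|---|
| 5% (2) | 2.0 points | 1.2 | 0.4 |
| 10% (5) | 5.1 | 3.1 | 1.0 |
| 20% (10) | 10.2 | 6.1 | 2.0 |
| 30% (15) | 15.3 | 9.2 | 3.1 |

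Worked cell: k = 5, p = 60% gives 5 × (0.90 − 0.60)/49 = 0.031. The same formula applies to ART uptake with s = 100%: at k = 5 and an uptake of 60% among the others, 5 × 0.40/49 = 4.1 points.

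**4. Effect on the Aim 3 contrast.** Assume suppression in genuinely untreated participants of 75% in accepters and 55% in decliners (a true difference of 20 points), and 90% in concealed participants. Each group's observed rate is (1 − c) × true + c × 0.90, where c is its concealed share.
- c = 20% in both: 78% − 62% = 16 points.
- c = 20% in accepters only: 78% − 55% = 23 points.
- c = 10% in accepters, 40% in decliners: 76.5% − 69% = 7.5 points.

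The direction therefore depends on where concealed participants fall, which the article cannot tell us.

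**The case against.** **Care status is a separate condition.** The Abstract and Discussion require infection and no engagement in care, and the Discussion and Aims 2 and 3 Design both speak of prevalent or incident infection. A reader might infer that the plan treats every Aim 1 positive as a new diagnosis outside care; it does not. A concealer must mislead twice, about status and then about care. That stands, but both checks rest on the same person's word.

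**A risk is not a count.** A reader might infer that concealed positives are in fact being counted as successes. The article gives no frequency, so only the possibility is established. At 10% concealed and p = 60%, the 3.1-point shift is small beside a 95% interval of about ±13.5 points at n = 49. However, a larger sample would not remove this error.

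**Aim 1 is largely untouched.** Randomization follows enrollment, so concealed positives should balance between arms, and yield of new diagnoses is not a listed outcome. This stands.

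**Few decliners.** About 5 people (54 − 49) may decline. A reader might infer a 40-point distortion from two concealed decliners (2/5). Any two people move a group of five that far, and the 49 is the target for viral load as well as navigation, so those 5 may have no viral load at all. The figure is no measure of concealment.

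**Payment.** The 17-fold ratio sets two visits, a survey, a blood draw and three recruits against one screening visit, and the article says its amounts match other local studies. The incentive is real, but the ratio is not its strength.

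**Detail may lie elsewhere.** Verification steps or a derived flag could sit in a fuller protocol or analysis plan. That is possible. The point here is narrower: the outcome as worded does not distinguish reaching suppression from arriving suppressed.

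**Conclusion.** The point holds as a limited one. As far as the article describes, prior diagnosis and current care are established by self-report, eligibility raises visit 1 pay from 1,000 to 9,000 kyat, and the ART and suppression outcomes are worded without use of the entry viral load. People already in care could enter Aims 2 and 3 and be credited as successes. The overstatement of suppression runs from about 0.4 to 15 points under the assumptions shown (5% to 30% concealed, 90% suppressed among them, 40% to 80% among the rest). The true frequency, and the direction of any bias in the Aim 3 contrast, cannot be determined from the document. The documents do not support a claim that the Aim 1 arm comparison is biased, nor that a corrected Aim 1 yield could be produced: viral load is offered only to those who accept CD4 point-of-care testing.

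**What to change.** 1. Use the scheduled month-0 viral load to flag participants suppressed at entry with no reported ART.
2. Define reaching viral suppression among participants unsuppressed at month 0.
3. Report ART initiation and the accept-versus-decline contrast with and without flagged participants.
4. At visit 2, repeat the questions on prior diagnosis and last HIV test within the existing questionnaire, stating that Aim 1 payment does not depend on the answer.
5. Describe Aim 1 positives as having no reported prior diagnosis, rather than as newly diagnosed, and claim no corrected Aim 1 yield.

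The cost is one derived variable, two repeated questions and one extra set of results. The flag is imperfect: it will catch a few natural controllers, miss people who are treated but unsuppressed, and shrink denominators slightly. That is why ART initiation and the contrast should be shown both ways.
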